### Sample

Women who are pregnant and smoke or who have quit smoking in the two weeks prior to their initial antenatal booking appointment will be eligible to participate. The inclusion criteria are pregnant or postnatal women, under the care of a midwife, who are either a current smoker (self-report or verified through CO reading of ≥ 7 ppm^2^) or ex-smoker (quit within two weeks prior to booking appointment). The exclusion criteria are pregnant women who are not smokers or who have reduced mental capacity.

### Sample size

We hypothesise that the flexible models of service delivery can increase the percentage of pregnant women who engage with smoking cessation services from 10 per cent (current rate of engagement in NHS England smoking cessation services) to 25 per cent. A sample size of 146 pregnant smokers in each group within each Health Board will allow a 15 per cent difference to be detected in the proportion of pregnant smokers who engage, with a five per cent type I error rate and 90 per cent power.

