### Interventions

The study will take place over 12 months using an integrated approach between maternity services, local public health teams and the NHS Stop Smoking Service. In each Health Board, an intervention and a usual care site will be selected from existing community midwifery teams. Sites will be selected on the basis of high rates of pregnant smokers, and a similar demographic profile in intervention and usual care sites within each Health Board. Pregnant smokers (i.e. those who are self-reported current smokers or have a CO reading # 7 ppm^b,^^c^ or who have quit in the two weeks prior to their booking appointment [5]) will be referred to the intervention or usual care NHS Stop Smoking Service on an opt out basis (see Figures 1 and 2). This automatically refers pregnant smokers to the service. The two main points for referral are the first antenatal appointment (at home or in a community antenatal clinic by the midwife) or subsequent scheduled antenatal care visits (by the midwife). However, the referral process can take place at any stage during pregnancy, for example, during the postpartum period whilst under the care of a midwife.

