### Analysis

Baseline demographic and social characteristics of pregnant smokers in both intervention and usual care sites will be summarised using descriptive statistics. Comparisons between the two groups will be carried out using a Student’s *t*-test or a non-parametric test for continuous data and a chi-squared test or a Fisher’s exact test for categorical data. Characteristics of women who do not opt out of the referral will be compared to those who do. Continuous data will be expressed as mean values with standard deviations and categorical data will be presented as counts with percentages. A single logistic regression model will be developed to obtain odds ratios for the comparison of different interventions with usual care, and for comparisons between interventions. Differences in baseline characteristics of individuals and referral rates for Stop Smoking Services will be adjusted for. To account for the geographical clustering of individuals, robust standard errors will be calculated.

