## Discussion

A quasi-experimental design for the proposed study was adopted as it was not logistically feasible to conduct a cluster randomised controlled trial in the desired timescales and within the available budget [15]. Although the randomised controlled trial is generally considered to have the highest level of credibility with regard to assessing causality, the use of a comparison group helps prevent certain threats to validity including the ability to statistically adjust for confounding variables.

The proposed study will address several areas where there are key evidence gaps relating to pregnant women and smoking cessation interventions. Specifically, how best to encourage pregnant women to attend a specialist stop smoking support service, how to deliver the service and who should provide it. The study will reveal important findings in relation to service delivery and enable local services to improve their effectiveness in a challenging area of public health. Ensuring better identification of pregnant smokers and providing access to timely support from smoking cessation specialists is crucial to reducing the number of women smoking during pregnancy in Wales. Investigating ways to provide a more flexible, women-centred approach is an important development which will assist in reducing the range of adverse factors for both mother and baby associated with maternal smoking behaviour.

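### The 90% power stated for 146 women per group in each Health Board holds only if women are independent, yet each group there is a single site and no allowance for clustering was made

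*Protocol article*

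**What the plan says.** The Sample size section of the protocol article expects engagement to rise "from 10 per cent (current rate of engagement in NHS England smoking cessation services) to 25 per cent". The claim that follows from this is: "A sample size of 146 pregnant smokers in each group within each Health Board will allow a 15 per cent difference to be detected". The operating characteristics attached to the claim are 5% type I error and 90% power. The section mentions no ICC, design effect or clustering.

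Allocation is by site. The Interventions section says: "In each Health Board, an intervention and a usual care site will be selected from existing community midwifery teams". It adds that each intervention site recruits one whole-time-equivalent worker to deliver the support.

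The Analysis section plans one logistic regression giving odds ratios for each intervention against usual care and between interventions, adjusted for baseline characteristics and referral rates. It adds: "To account for the geographical clustering of individuals, robust standard errors will be calculated".

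The Discussion explains the quasi-experimental design by saying that "it was not logistically feasible to conduct a cluster randomised controlled trial".

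**The concern.** The analysis treats women at the same site as correlated, but the sample size treats them as independent. Women at one site share a midwifery team and a local population, and at intervention sites they share the post that delivers the support. Their engagement is therefore likely to be correlated to some degree, and any positive correlation lowers the information in 146 women per site.

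There is a second difficulty. With one site per group, a difference between the two sites of a Health Board cannot be told apart from an effect of the intervention, however many women are counted.

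The study is meant to inform how the service should be delivered and by whom. A 90%/5% claim attached to each Health Board could lead readers to take a null result there as evidence of no effect, and a significant one as proof for the model used there.

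**Working it through.** **Inputs.** From the Sample size section: p1 = 0.10, p2 = 0.25, difference 0.15, alpha 0.05, power 0.90, 146 per group. From the Interventions section: one site per group in each Health Board. From the Methods opening: four Health Boards, hence eight sites. Assumed, because the documents give none: ICC from 0.001 to 0.05. Two-sided testing is also assumed; the section does not say, but it is what reproduces 146.

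**Step 1: reproduce 146.** With mean proportion 0.175:

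n = [1.960·√(2·0.175·0.825) + 1.282·√(0.10·0.90 + 0.25·0.75)]² / 0.15² = (1.0532 + 0.6751)² / 0.0225 = 132.8.

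With continuity correction: n = (132.8/4)·[1 + √(1 + 4/(132.8·0.15))]² = 145.8, which rounds up to 146. Power at 146 is 90.0% with the correction and 92.5% without it. Other common versions do not match: 133 two-sided uncorrected, 109 or 121 one-sided, 130 unpooled, 129 arcsine. The arithmetic is right, and the design effect in it is 1.

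**Step 2: allow for one site per group.** Design effect = 1 + (146 − 1)·ICC; effective n = 146 / design effect. The power formula of step 1 is then applied to the effective n. At ICC 0.01, for example:

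- Design effect 2.45, effective n 59.6.
- z = (0.15 − 1.960·0.0696)/0.0682 = 0.20, so power is 58%.
- Subtracting 1/59.6 in the numerator for the continuity correction gives 48%.

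| Assumed ICC | Design effect | Effective n | Power, uncorrected | Power, corrected |
|---|---|---|---|---|
| 0.001 | 1.15 | 127.5 | 89% | 85% |
| 0.002 | 1.29 | 113.2 | 85% | 80% |
| 0.005 | 1.73 | 84.6 | 73% | 66% |
| 0.01 | 2.45 | 59.6 | 58% | 48% |
| 0.02 | 3.90 | 37.4 | 40% | 29% |
| 0.05 | 8.25 | 17.7 | 21% | 11% |

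The table treats between-site variance as known. With one site per group it cannot be estimated within a Health Board, so these figures illustrate the loss; they are not the power of a test that could be run there.

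**Step 3: could more women per site restore 90%?** Effective n cannot exceed 1/ICC. At ICC 0.01 the ceiling is 100, below the 133 (uncorrected) or 146 (corrected) needed, so no site size is enough. At ICC 0.005 the number per site would be n₀(1 − ICC)/(1 − n₀·ICC): 396 for n₀ = 133 and 539 for n₀ = 146.

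**Step 4: type I error if clustering were ignored.** 2·[1 − Φ(1.960/√design effect)] gives about 14%, 21%, 32% and 50% at ICC 0.005, 0.01, 0.02 and 0.05.

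**Step 5: pooled contrast over four site pairs.** Standard error = √[(0.09 + 0.1875)·design effect/(146·4)], referred to a non-central t with 3 df (critical value 3.182). At ICC 0.01 this is 0.0341, non-centrality 0.15/0.0341 = 4.40, power 82%. Over the range:

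| Assumed ICC | 0.001 | 0.002 | 0.005 | 0.01 | 0.02 | 0.05 |
|---|---|---|---|---|---|---|
| Pooled power | 98% | 97% | 92% | 82% | 65% | 38% |

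This assumes the same 15-point difference in every pair.

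**The case against.** The strongest reply is that the shortfall depends on an ICC the documents do not give. That stands. A reader might infer that the design falls well short of 90% under any realistic clustering, and the documents do not support this: at ICC 0.001 uncorrected power is 89%. Sites are chosen within a Health Board for similar demographic profiles, and the model adjusts for baseline characteristics and referral rates. Both may lower the residual ICC, though by an unstated amount, and neither can remove a site effect or the effect of a single worker.

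A reader might also infer that the planned analysis has a type I error of up to 50%. It does not follow. The figures in step 4 belong to a test that ignores clustering, whereas the plan specifies robust standard errors. Those have only eight sites to work with, and no replication within a Health Board, but how well they perform is a separate question.

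Nor is it right that the powered comparison is simply not the analysed one. The single regression estimates each intervention against usual care and names no pooled contrast. With three models over four intervention sites, at least two models rest on one site each if all three are used, so those contrasts lie close to the per-Health-Board ones.

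The Discussion is open that the design is quasi-experimental, and no passage proposes to over-read Health Board results. Both points are fair, but neither corrects the power statement. An unseen analysis plan could not correct it either: 146 is fully used up by the formula for independent individuals.

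**Conclusion.** The power statement is wrong as written. The calculation of 146 is correct for independent women, but that is not the design described. Using the continuity correction that yields 146, power within a Health Board falls below 90% for any ICC above zero; without the correction it does so above about 0.0007. Across the assumed range of 0.001 to 0.05 it runs from 89% down to 21% uncorrected, and from 85% down to 11% corrected.

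The size of the loss rests on the assumed ICCs, equal sites of 146 and between-site variance treated as known. Two conclusions need no particular ICC value: the figure carries no clustering allowance, and within a Health Board a site or single-worker effect is confounded with the intervention.

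**What to change.** In the Sample size section, either withdraw the per-Health-Board statement of 90% power and 5% type I error, or state that it holds only if women are independent and set the step 2 range of ICCs beside it, small values included. Present per-Health-Board comparisons, and comparisons of a model delivered at a single site, as estimates with intervals and no power claim.

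If a powered comparison is wanted, two changes go together: name the pooled contrast of flexible models against usual care over the four site pairs in the Analysis section, which does not name it now, and state its power over an ICC range as in step 5. Giving the power without naming the contrast would create a new mismatch.

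No extra recruitment or data are required. The cost is rewording, one added contrast if that option is taken, and a less favourable stated power.

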### Quantitative data collection

Quantitative data collection will principally utilise routine data from: i) the Health Board’s electronic Patient Administration System (PAS) and Maternity Information System, which contain information about expectant mothers smoking status and birth outcomes and ii) the NHS Stop Smoking Service database which will record referral and treatment information for all intervention and usual care clients. Each Health Board uses a national standardised maternity record. The maternity record aims to improve quality and safety of maternity care and is updated regularly according to national guidelines to represent the latest recommendations for best practice. Within the record, there is a comprehensive risk assessment which identifies individual risk factors, including smoking status, for the expectant mother. Data from the patient hand-held record is entered into each Health Board’s electronic PAS and Maternity Information System (where available). Additional file 1 provides detail about the specific data items to be extracted from the PAS and Maternity Information System for this study.

Information about the referral pathway and stop smoking treatment programme will be entered onto a separate database used by the existing NHS Stop Smoking Service which has recently undergone developments including the ability to conduct e-referrals. Data items to be extracted are detailed in Additional file 1. To facilitate this process, Memoranda of Understanding (MoU) will be established between Public Health Wales Informatics team and the four participating Health Boards and between Public Health Wales Informatics and the NHS Stop Smoking Service which will allow Public Health Wales to hold and process Health Board and NHS Stop Smoking Service data on their behalf. Approval will be sought from each Health Board and the NHS Stop Smoking Service to allow Public Health Wales Informatics to release anonymised data to specified analysts for use in accordance with an agreed analysis plan. The Public Health Wales Informatics team will act as the NHS Stop Smoking Service’s and the Health Board’s agent in this process and undertake any linking that has to be undertaken before anonymising the data and providing it to analysts. All data will be anonymised, therefore patient confidentiality will be maintained. All documents will be stored securely and only accessible by study staff and authorised personnel. The study will comply with the Data Protection Act which requires data to be anonymised as soon as it is practical to do so.

### Analysis

Baseline demographic and social characteristics of pregnant smokers in both intervention and usual care sites will be summarised using descriptive statistics. Comparisons between the two groups will be carried out using a Student’s *t*-test or a non-parametric test for continuous data and a chi-squared test or a Fisher’s exact test for categorical data. Characteristics of women who do not opt out of the referral will be compared to those who do. Continuous data will be expressed as mean values with standard deviations and categorical data will be presented as counts with percentages. A single logistic regression model will be developed to obtain odds ratios for the comparison of different interventions with usual care, and for comparisons between interventions. Differences in baseline characteristics of individuals and referral rates for Stop Smoking Services will be adjusted for. To account for the geographical clustering of individuals, robust standard errors will be calculated.

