**Recruitment flow diagram.**

In intervention sites, pregnant smokers will be referred to one of three different models of service delivery where smoking cessation services are provided by maternity support workers, midwives or smoking cessation advisors dedicated to working with pregnant women, all offering a flexible service designed to meet the needs of the women. The core elements of the evidence base to be implemented in all intervention sites will include:

 Strict adherence to NICE opt out smoking cessation pathway for pregnant women, including CO monitoring. Smoking cessation services being more closely aligned to maternity services (provided as part of the package of maternity care). Referral from midwife to smoking cessation support within 48 hours Flexibility in service model with a women centred approach.

Each intervention site will recruit a whole-time equivalent (WTE) maternity support worker (employed by the Health Board), midwife (employed by the Health Board) or dedicated Stop Smoking Advisor for pregnant women (employed by the NHS Stop Smoking Service) who will deliver stop smoking support to pregnant women. These staff will receive referrals directly from midwives to provide an intensive smoking cessation intervention at times and settings of the women’s choice, including home visits. During every subsequent antenatal appointment, women will be asked about their smoking status and referred as appropriate. If a woman has declined treatment (i.e. she opts-out by not answering the telephone to stop smoking services or refuses an assessment appointment) she will be asked if she would like to be re-referred during each follow-up appointment.

Clients in intervention sites will be offered smoking cessation support for the duration of their pregnancy if required. The support they receive will follow an adapted behavioural intervention model documented in the NHS Stop Smoking Service delivery manual, which is based on withdrawal oriented therapy (Maudsley model) [12]. This may involve a combination of telephone and face to face support as well as motivational support by email and or text, dependent upon the needs of the client (see Figure 1). A detailed manual for specialist smoking cessation staff has been developed for use in all intervention sites detailing the referral pathway, intervention programme, policies, procedures and support materials.

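### The logistic model lists no Health Board term, so differences in baseline engagement between Health Boards can pass into the odds ratios for the service models

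*Protocol article*

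**What the plan says.** All references are to the protocol article.

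- **Interventions, site selection.** "In each Health Board, an intervention and a usual care site will be selected from existing community midwifery teams". The sites are to have high rates of pregnant smokers and "a similar demographic profile in intervention and usual care sites within each Health Board". The Methods section describes the four Health Boards as self-selected and geographically diverse.
- **Interventions, service models.** In intervention sites, "pregnant smokers will be referred to one of three different models of service delivery". Each site recruits one whole-time equivalent of one provider type: maternity support worker, midwife or dedicated advisor.
- **Sample size.** The hypothesis is a rise in engagement "from 10 per cent (current rate of engagement in NHS England smoking cessation services) to 25 per cent". The number needed to detect this is put as "A sample size of 146 pregnant smokers in each group within each Health Board", which is meant to do so "with a five per cent type I error rate and 90 per cent power".
- **Analysis.** A single logistic model is to give "odds ratios for the comparison of different interventions with usual care, and for comparisons between interventions". The stated adjustment covers individual baseline characteristics and referral rates. Geographical clustering is handled by robust standard errors. Health Board does not appear as a model term, a stratification factor or a paired contrast.
- **Discussion.** The evidence gaps to be addressed include "how to deliver the service and who should provide it".

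**The concern.** The design and the sample size both rest on comparing an intervention site with the usual care site in the same Health Board. Read plainly, the analysis sets each model against one usual-care category drawn from all four Health Boards.

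Three models over four intervention sites, with one provider type per site, means that two models run in one Health Board each and the third runs in two. A model is therefore tied to the general level of engagement where it was placed. Without a Health Board term, a model placed where engagement is high for other reasons looks better than it is, and one placed where engagement is low looks worse. Comparisons between models inherit the same distortion.

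Robust standard errors change the estimated variance but leave the point estimate as it is. At stake are the estimates for the primary outcome and any ranking of provider types.

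**Working it through.** **1. The plan's own figure.** Inputs from the Sample size section: 10% vs 25%, type I error 5%, power 90%. Two-sided testing is assumed because it reproduces the stated number.

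- Mean proportion = (0.10 + 0.25)/2 = 0.175.
- Uncorrected n = [1.960 × √(2 × 0.175 × 0.825) + 1.282 × √(0.10 × 0.90 + 0.25 × 0.75)]² / 0.15² = 132.8, so 133.
- Continuity-corrected n = (132.8/4) × [1 + √(1 + 4/(132.8 × 0.15))]² = 145.8, so 146.

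The stated 146 is reproduced. It is the size of a two-group comparison inside one Health Board.

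**2. Bias when no model has any effect.** The article gives no engagement rates by Health Board, so these are assumptions: 10% in three Health Boards, a higher rate in the fourth, and equal numbers per site. Odds = p/(1 − p).

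- Fourth at 15%: pooled usual care = (3 × 0.10 + 0.15)/4 = 0.1125. A model run only there shows OR = (0.15/0.85)/(0.1125/0.8875) = 1.39.
- In the same setting, a model run only in a 10% Health Board shows (0.10/0.90)/(0.1125/0.8875) = 0.88. The between-model OR is (0.15/0.85)/(0.10/0.90) = 1.59.
- Fourth at 20%: pooled usual care = 0.125, and OR = (0.20/0.80)/(0.125/0.875) = 1.75.
- If the higher-rate Health Board is one of two running the same model, the bias is smaller. At 15%, that model's rate is (0.15 + 0.10)/2 = 0.125 and OR = (0.125/0.875)/(0.1125/0.8875) = 1.13. At 20%, the rate is 0.15 and OR = (0.15/0.85)/(0.125/0.875) = 1.24.
- If all four rates are equal, every OR is 1.00.

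**3. Bias when every model has the same true effect.** A logistic model was fitted to expected proportions, with 146 per site and a within-Health-Board OR of 3.0 (10% vs 25%). Assumed allocation: model A in Health Boards 1 and 4, B in 2, C in 3.

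| Usual-care rates, Health Boards 1–4 | A, B, C without Health Board term | A, B, C with Health Board term |
|---|---|---|
| 10, 10, 10, 10% | 3.00, 3.00, 3.00 | 3.00, 3.00, 3.00 |
| 8, 10, 12, 10% | 2.66, 3.00, 3.68 | 3.00, 3.00, 3.00 |
| 5, 10, 15, 10% | 2.15, 3.00, 4.76 | 3.00, 3.00, 3.00 |

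Models with identical effects would be ranked by place. The model with Health Board indicators has 7 parameters and design rank 7, so it can be estimated.

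**4. Price in precision.** Take 10% vs 25% throughout and the model-based SE of the log OR, before clustering.

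- One-Health-Board model, no Health Board term (584 usual-care women): √[1/(584 × 0.09) + 1/(146 × 0.1875)] = 0.24.
- The same model with the term (146 usual-care women): √[1/(146 × 0.09) + 1/(146 × 0.1875)] = 0.34.
- Power with the term: ln 3.0/0.336 − 1.96 = 1.31, which corresponds to about 90%.
- For the model in two Health Boards, the SE rises from 0.19 to 0.24.
- Contrast of two single-Health-Board models: from √[2/(146 × 0.1875)] = 0.27 without the term to √(0.336² + 0.336²) = 0.47 with it.

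**The case against.** The strongest reply is that the gap is read from silence. The article does not say that Health Board is left out or that usual care is pooled. It says that a model will be developed, it names no individual covariate, and its data collection section refers to an agreed analysis plan that is not shown. This stands as a caution: the full plan may already contain the term. It does not dispose of the point, because the Analysis section does state the contrasts, the kinds of adjustment and the handling of geography, and followed as written it produces the bias shown.

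It can also be said that individual covariates and referral rates may absorb some Health Board differences, and that demographic similarity of paired sites still helps the overall balance. That is fair. A reader might infer that the within-Health-Board selection is wholly wasted, and the documents do not support this. But referral rate is not baseline engagement, and the similarity sought is demographic only.

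Three further inferences go too far:

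- **That no analysis can separate provider type from Health Board.** Each Health Board has its own usual care site, so differences shared by both its sites can be removed from between-model contrasts too. What remains is confounding with site and staff. Nor does the article say that one person fills each post, since one whole-time equivalent can be shared.
- **That the sample size fails because between-model power is low.** The article claims no power for those contrasts.
- **That the 5% error rate is breached because several contrasts are listed.** Multiplicity is a separate matter that an article may leave to its analysis plan.

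**Conclusion.** The point holds as a conditional bias in the model as described. If usual-care engagement differs between Health Boards beyond what the listed covariates capture, the odds ratios for individual models, and those between models, absorb the difference. Under the assumed 15% vs 10% rates and no true effect, a model run in one Health Board shows an OR of 1.39, or 1.13 if that Health Board is one of two running the model. Under usual-care rates of 8% to 12% and a common true OR of 3.0, the apparent values run from 2.66 to 3.68.

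These sizes rest on assumed rates and an assumed allocation of models to Health Boards, and the bias is zero if rates are equal. The documents do not show that such differences exist, so a reader should not conclude that the results will be biased by any given amount. A Health Board term removes only what the two sites of a Health Board share. Differences between those two sites, and between the staff at them, remain.

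**What to change.** Add three Health Board indicators to the logistic model, so that each service model is compared with the usual care site in its own Health Board, and say so in the Analysis section. If the analysis plan already has this term, a sentence in the article is enough. The extracts come from each Health Board's own systems, so no new data should be needed.

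Label the between-model odds ratios as exploratory. State that, even with the Health Board term, provider type cannot be separated from site and staff effects for a model run at a single site.

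The cost is precision: a log-OR standard error of about 0.34 rather than 0.24 for a model in one Health Board. That is the precision on which the 146 per group was planned, before any allowance for clustering. Contrasts between models lose more, which is a further reason to treat them as exploratory.
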